### Molecular analyses

A subgroup of participants will undertake muscle biopsies (n = 30). This sample size was estimated using data from previous studies [79] in which muscle fibre type [26, 28], MRF (i.e., myostatin, MyoD) [26, 32], and phosphorylation of p70S6K [32, 80] increased after training interventions (i.e., aerobic and resistance training). Thus, based on effect sizes ranging from 1 to 2.5 from those studies and an α level of 0.05 and a power (1-β) of 0.8, it was found that eight patients per group would be sufficient. To account for a possible 30% dropout, we will recruit ten patients per group in this study. Muscle biopsies will not be performed on individuals on anti-platelet or anti-coagulation therapy [81].

#### Muscle biopsy

Patients will attend the Laboratory at 8:00 a.m. after overnight fasting without carrying out any type of exercise in the previous 48 h. Muscle samples will be obtained on the vastus lateralis of the non-dominant leg by an experienced medical doctor using the modified Bergstrom needle technique with suction following suggested procedures in a similar population [82]. Muscle samples will be separated from any fatty tissue and blood, and divided into portions that will be treated for specific analyses. Muscle samples (~ 80 mg specimen) will be divided into five parts 1) fibre type isolation (20 mg), 2) microRNAs (20 mg), 3) mRNA expression (10 mg), 4) fibre type morphology (10 mg), and 5) whole muscle protein expression by Western blot (20 mg) analyses. All samples will be stored at − 80 °C until analysis.

### Single muscle fibre isolation

Muscle samples will be freeze-dried in a tissue lyophiliser for 48 h. Next, a small segment (~ 3 µm) will be dissected under a light microscope using forceps and collected into a 10 µl loading buffer (1 × Lammelli’s buffer containing 10% β-mercaptoethanol), and stored overnight at − 80 °C. 30–60 single fibre segments will be collected from each sample as optimised previously [83]. Muscle fibre typing will be assessed by dot blotting. For each subject sample, a minimum of 9 muscle fibre segments will be pooled before electrophoresis.

Whole homogenate muscle specimen and isolated fibre type pools (type I, IIa and IIx) for the canonic protein synthesis Akt/mTOR/S6K1/rpS6 pathway, myogenic regulatory factors (Myogenin, MyoD, myf5, MRF4, and myostatin) and degradation (autophagy; LC3, p62, Parkin, beclin and ubiquitin–proteasome system; MuRF-1, atrogin-1, Need-1/4) systems will be analysed. Furthermore, NF-kB and MAPK pathways will also be explored for a relationship between inflammation and degradation systems. The protein content will be evaluated by Western blotting, and mRNA expression will be assessed by real-time qPCR before and after training.

### Muscle and plasma microRNAs

MicroRNAs will be isolated from plasma samples using the miRNeasy mini kit (Qiagen, CA) and from skeletal muscle tissue samples using the mirVana miRNA Isolation Kit (Life Technologies, USA) according to the manufacturer's instructions. Synthetic spike-in (UniSp3, UniSp4, UniSp5, UniSp6) and synthetic C. elegans miRNA (Cel-miR-39 and Cel-miR-54) will be used to analyse the robustness of the RNA isolation process and quality of isolated microRNA for muscle and plasma samples, respectively. Both extracted RNA will be subjected to Reverse Transcriptase PCR using the TaqMan MicroRNA Reverse Transcription Kit (Applied Biosystems). MicroRNA levels will be measured by real-time PCR amplification using TaqMan MicroRNA Assays specific for miR-1, miR-133, miR206, miR29b, miR-486, miR-499, miR-542, miR-181, miR-133a, miR-27a, miR-181a, miR-208 (Applied Biosystems), according to the manufacturer's instructions. We will also use the red blood cell-specific miR-451 and the stable miR-23a to monitor haemolysis in plasma samples. Furthermore, the results will be normalised to the exogenous spiked in control previously described for each sample.

### Muscle fibre morphology

Muscle sample will be prepared using isopentane snap freezing for immunohistochemical staining for fibre type identification. Overnight incubation will be conducted with the primary antibodies: dystrophin rabbit polyclonal antibody (1:200) (Thermo Scientific, China) and α-II spectrin rabbit polyclonal antibody (1:400), to target the cell membrane and the mouse monoclonal antibody for myosin heavy chain (MyHC, 1:400) to target type II myofibers. After confocal microscopy imaging, fibre type identification and CSA of fibres will be performed automatically using the free available software Fiji-ImageJ (NIH) following previous recommendations [84].

### Statistical analysis

The primary analysis will follow an intent-to-treat approach. A two-way analysis of variance (ANOVA) will be used to compare the three intervention groups and time (Pre- and Post-). If an interaction effect is found, a Tuckey´s post hoc test will be used for pairwise comparisons. Differences will be considered statistically significant at the 0.05 level (two-sided).

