### Experimental approach

We will compare the effects of CONC, ECC and the combination of CONC + ECC training on the changes in exercise performance (aerobic capacity and muscle strength), muscle mass, functional performance, levels of physical activity, quality of life, changes in biomarkers of cardiometabolic health (insulin resistance and lipid profile) and systemic inflammation. The proposed study is a multicentre randomised trial that will employ a 3 (groups) × 2 (measure times: Pre- and Post-) repeated measures design. The total duration of the proposed study is 14 weeks, including a 12-week training period and a testing week before and after the intervention. A stratified randomised assignment upon sequential number (by block) process will ensure that the experimental groups are balanced for FEV_1_, sex, and age. The allocation sequence will be performed by the multicentre coordinator. The training sessions will be conducted at three clinical centres in Santiago, Chile (Instituto Nacional del Torax, Hospital Clinico Universidad de Chile, Hospital Clinico Universidad Catolica). Assessors of all outcomes will be blinded to the group allocation of participants, which will not be revealed during the participation of the study.

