### Participants

Sixty-six participants diagnosed with severe COPD (FEV_1_ < 50% of predicted; quartiles 3 and 4 in the BODE [Body-mass index, airflow Obstruction, Dyspnoea, and Exercise] index) will be recruited via newspaper advertisements, posters, flyers, visits to local community centres and referral from associated centres. The sample size calculation revealed that based on an α level of 0.05 and a power (1-β) of 0.8, and effect sizes ranging from 0.6 to 1.2 found in similar outcomes (muscle CSA, 6MWT) in our preliminary data after eccentric training, and few studies using combined eccentric and concentric cycling [67–69], a minimum of 17 patients would be necessary per group for this study. However, 22 patients per group will be recruited to account for a typical dropout rate of 30% in long-term training studies. Accredited Ethics Committees from all three Hospitals and universities have approved this study. Any important modification will be informed to the ethics committees. All participants will obtain medical permission from a pulmonary medical specialist before taking part in the study. Exclusion criteria will be: current insulin therapy, long-term oxygen therapy, asthma, other concomitant pulmonary diseases, or other diseases that could affect physical activity [70, 71]. Participants will be instructed to continue with normal everyday activities yet be dis-encouraged from engaging in any unaccustomed training or supplementary nutrition and will be fully informed of the nature and possible risks of all of the experimental procedures before providing their written informed consent. Written informed consent will be obtained from the multicentre coordinator. Criteria for discontinuing intervention will be upon participant request or worsening disease. Patients will receive an initial report for all their clinical assessments, which will be upgraded at the end of the study participation. Participants will be coded as sequential number upon recruitment. A Data Monitoring Committee (DMC) will not be necessary as it will be a short intervention and with sample size that can be handle by the research team. Adverse events will be collected and reported appropriately. All personal information will be coded, and data collected will be kept confidential, and only the PI and multicentre coordinator of this study will have access to the files. The computer will be held in the PI office.

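### The primary analysis is labelled intent-to-treat, but the only model named, a Pre/Post group-by-time ANOVA, tests the arms on patients with both values only

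*Protocol article*

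**What the plan says.** **Label and model.** The Statistical analysis section states: "The primary analysis will follow an intent-to-treat approach". It then names one model: "A two-way analysis of variance (ANOVA) will be used to compare the three intervention groups and time (Pre- and Post". Pairwise comparisons follow only if the interaction is found. No other model and no imputation is mentioned.

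**Design.** The Experimental approach section describes a "3 (groups) × 2 (measure times: Pre- and Post-) repeated measures design", with one testing week before and one after 12 weeks of training. There is a single post-baseline test.

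**Expected loss.** The Participants section sets the size "based on an α level of 0.05 and a power (1-β) of 0.8". It concludes that "a minimum of 17 patients would be necessary per group for this study" and that "22 patients per group will be recruited to account for a typical dropout rate of 30% in long-term training studies". The total is given as "Sixty-six participants diagnosed with severe COPD".

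**Why patients stop.** The same section says: "Criteria for discontinuing intervention will be upon participant request or worsening disease". It does not say whether a patient who stops training is still tested at Post.

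**The concern.** The label promises that all randomised patients are compared in the arm to which they were allocated. The named model takes its between-arm test only from patients with a complete Pre/Post pair. The two agree only if nearly everyone has a Post value, and the protocol plans for the opposite.

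Two things are at stake. The first is description: a complete-pairs result would be reported as intent-to-treat, and the Discussion expects the results to inform national COPD management guidelines. The second is validity: worsening disease is an outcome-related reason to stop, so patients with pairs may not represent those randomised. If that selection works differently in the three arms, the comparison of arms is biased.

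**Working it through.** **1. The plan's own figures.** For two means, two-sided α 0.05 and power 0.80, the normal approximation is n = 2(1.96 + 0.8416)²/d². At d = 1.0 this is 15.7, and the t-test version is 16.7, which rounds up to 17. So 17 per group is reproduced at d of about 1.0, inside the stated range of 0.6 to 1.2, although the article does not say which value was used. The 22 is reproduced as 17 × 1.30 = 22.1.

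**2. What the interaction test uses.** With two times, the group-by-time F test is the one-way ANOVA of D = Post − Pre across the three groups. A patient without Post has no D. With n complete pairs the test has 2 and n − 3 degrees of freedom.

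**3. Planned loss.**
- Without Post: 0.30 × 66 = 19.8, about 20 patients.
- Complete pairs: 66 − 19.8 = 46.2, about 46, or 46.2/3 = 15.4 per group.
- Error degrees of freedom: 66 − 3 = 63 with everyone, about 46 − 3 = 43 with pairs only.

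This is the loss if every planned dropout misses Post.

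**4. How far the comparison could move (inputs assumed, none from the article).**

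*Illustration A: unequal dropout.* Completers in two arms both improve by 0.8 SD, dropouts improve by 0, and dropout is 20% in one arm and 40% in the other.
- All randomised: 0.8 × 0.80 = 0.64 and 0.8 × 0.60 = 0.48, a difference of 0.16 SD.
- Complete pairs: 0.8 − 0.8 = 0.

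With equal 30% dropout each arm's mean change is overstated by 0.30 × 0.8 = 0.24 SD. That cancels between arms and affects only within-arm changes.

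*Illustration B: equal dropout, different mechanism.* Two arms of 22, change SD 1, no true difference, average loss 30% in each. In one arm the loss is random; in the other it is 50% among patients with a negative change and 10% among the rest. A half-normal variable has mean 0.798, so the mean change among those kept in the second arm is (0.5 × 0.9 × 0.798 − 0.5 × 0.5 × 0.798)/0.70 = 0.23 SD. In 4000 simulated trials the mean spurious difference was 0.23 SD, and 9.7% were significant against a nominal 5%.

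**5. What a likelihood model would change.** With one post-baseline visit the likelihood splits into a part for Pre and a part for Post given Pre and arm. A patient without Post informs only the first part. The estimated arm difference is therefore close to a completers' ANCOVA, valid if Post is missing at random given baseline. In illustration A, with dropout unrelated to baseline, it would still give about 0. No-change imputation would return 0.16, but only because the illustration sets dropouts' change to 0.

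**The case against.** The strongest reply is that the article states a principle and a model, and leaves missing Post values to a full protocol or SAP that is not shown. Group-by-time terms can be fitted by likelihood or on imputed data, and intent-to-treat also means analysis by allocated arm. This has weight: a later document could rescue the label, and the absence of a missing-data section is not the point made here. What remains is that the article does name a method, and that method does not by itself deliver the population it declares. Whether patients who stop training are tested at Post is also a matter of conduct that no later analysis can recover.

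A reader might infer more than the article supports, in four ways.
- *That about 20 patients will be excluded.* The 30% is a planning rate, and the stopping rule concerns the intervention, not assessment.
- *That raising 17 to 22 proves a completers' analysis.* Trials that analyse everyone also inflate for lost information.
- *That tolerability, and so dropout, will differ by arm.* The Background reports lower cardiopulmonary and perceptual demand for eccentric cycling, but Training protocols gives CONC and ECC the same perceived-exertion target of 14, and no difference in dropout is predicted.
- *That a mixed model would cure the problem.* Step 5 shows that it would not.

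It is also fair to say that Post testing includes MRI and an exercise test to exhaustion, which some patients who stopped for worsening disease may not complete.

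**Conclusion.** The point holds as a conflict between the stated label and the stated model. As written, the between-arm test is a complete-pairs analysis under an intent-to-treat name. Up to about 20 of 66 randomised patients would fall outside it at the planned dropout rate, fewer if those who stop training return for Post.

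The loss may be related to outcome, given the stated reasons for stopping. The article does not establish that it differs by arm, or that the comparison will be biased. The 0.16 SD and 0.23 SD figures rest wholly on assumed inputs: they show that a bias of that order is possible, not that it is expected. The change should be made, since it is cheap and part of it must be settled before patients stop training.

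That 22 per group less 30% leaves 15.4 rather than 17 is a separate sizing matter and is not needed for this conclusion.

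**What to change.** 1. **Follow-up.** State that patients who stop training are asked to attend the existing Post testing week, for whichever tests they can complete, and are analysed in their allocated arm.
2. **Primary model.** Replace the ANOVA with a baseline-adjusted likelihood model: Pre and Post as outcomes, a common baseline mean, arm-by-Post terms, and the stratification factors in Experimental approach (FEV1, sex, age). Include every randomised patient with a baseline. State that it assumes missing at random given baseline and does not by itself correct outcome-dependent dropout.
3. **Sensitivity.** Add one analysis for outcome-dependent missingness, such as no-change imputation of missing Post values.
4. **Label.** Report the present ANOVA as a complete-case analysis.

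Items 1 and 3 do most of the work against outcome-dependent loss; item 2 makes the model and its assumption explicit. The cost is analysis wording and some additional Post tests, not all of which every patient can complete. The estimated effect may also be smaller.

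### The planned group-by-time ANOVA is a valid but unadjusted comparison of changes: it leaves out the baseline covariate and the stratification factors FEV1, sex and age, and so loses precision

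*Protocol article*

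**What the plan says.** All quotes are from the protocol article.

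- **Model** (Statistical analysis): "A two-way analysis of variance (ANOVA) will be used to compare the three intervention groups and time (Pre- and Post". No covariate is named.
- **Pairwise step** (same section): "If an interaction effect is found, a Tuckey´s post hoc test will be used for pairwise comparisons". The sentence does not say which means are compared.
- **Significance** (same section): "Differences will be considered statistically significant at the 0.05 level (two-sided".
- **Design** (Experimental approach): "3 (groups) × 2 (measure times: Pre- and Post-) repeated measures design".
- **Randomisation** (Experimental approach): "A stratified randomised assignment upon sequential number (by block) process will ensure that the experimental groups are balanced for FEV_1_, sex, and age".
- **Centres** (Experimental approach): "The training sessions will be conducted at three clinical centres in Santiago, Chile". Centre is not listed among the stratification factors.
- **Size** (Participants): at least 17 patients per arm are needed; 22 per arm, 66 in all, are to be recruited to allow for 30% dropout.

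**The concern.** The trial measures each outcome before and after training and stratifies randomisation on three patient characteristics. The stated model then treats the Pre value only as one of two levels of a time factor and has no term for FEV1, sex or age. This gives up precision in two ways.

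- **Baseline.** Subtracting the Pre value fixes its coefficient at 1. ANCOVA estimates the coefficient, and the residual variance is smaller unless that slope happens to be 1.
- **Stratification factors.** Stratification balances the arms on FEV1, sex and age, so these factors contribute less to chance differences between arms. If they predict the outcome and are left out, their variation stays in the error term. The standard error then overstates the true uncertainty, and the test is conservative.

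At stake is the ability to separate three active arms with about 17 completers each. The article hopes to show that combined training does better than either mode alone. There is no untrained control arm, so that claim rests entirely on between-arm differences.

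**Working it through.** **The plan's own figures.** The article gives no variance or Pre-Post correlation, so it has no figure for this point to reproduce. The 17 per arm comes from an effect-size range, not a single value, and has no unique reproduction. It is used below only as the number analysed. (17 × 1.3 = 22.1 matches the 22 recruited.)

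**Step 1: what the interaction tests.** With two repeated measurements, the group-by-time contrast between arms A and B is (Post − Pre in A) − (Post − Pre in B). The interaction F is therefore the one-way ANOVA F on the change scores, with 2 and 51 − 3 = 48 degrees of freedom at 17 per arm. A check on simulated data gave F = 5.848 by both routes. In 4,000 simulated trials at each correlation (0.5, 0.7, 0.9), its type I error was between 4.5% and 5.6%. The test is valid and does use the baseline, by subtraction.

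**Step 2: cost of not using baseline as a covariate.** Let s be the SD at both times and r the Pre-Post correlation. Both are assumptions.

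- Change score: Var = 2(1 − r)s²
- ANCOVA: Var = (1 − r²)s²
- Ratio = (1 − r)(1 + r) / [2(1 − r)] = (1 + r)/2

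| Assumed r | Change (s²) | ANCOVA (s²) | Ratio | Change-score n per arm that matches 17 under ANCOVA |
|---|---|---|---|---|
| 0.5 | 1.00 | 0.75 | 0.75 | 17/0.75 = 22.7 |
| 0.7 | 0.60 | 0.51 | 0.85 | 17/0.85 = 20.0 |
| 0.8 | 0.40 | 0.36 | 0.90 | 17/0.90 = 18.9 |
| 0.9 | 0.20 | 0.19 | 0.95 | 17/0.95 = 17.9 |

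If the SDs differ (s₀ at Pre, s₁ at Post), the change-score variance minus the ANCOVA variance is s₀² − 2r·s₀s₁ + r²s₁² = (s₀ − r·s₁)². This is never negative, so the direction does not depend on equal SDs. The small loss from estimating the slope is ignored here.

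**Step 3: effect on power.** Simulation with 17 per arm, Post means at 0, 0.3 and 0.6 SD (assumed), and the omnibus test at 0.05:

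| Assumed r | Group-by-time interaction | ANCOVA on baseline |
|---|---|---|
| 0.5 | 31% | 39% |
| 0.7 | 49% | 55% |
| 0.9 | 94% | 94% |

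**Step 4: stratification factors.** If FEV1, sex and age explain a share p of the remaining variance, adjustment multiplies that variance by about 1 − p. The article gives nothing from which p could be taken, so this gain is left without a number.

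**Step 5: price in degrees of freedom.** At 51 completers the change-score comparison leaves 48. Adding baseline, FEV1, sex and age as one term each leaves 51 − 3 − 4 = 44. Centre would take two more, leaving 42.

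**The case against.** The best defence is that the planned test is correct. Change-score analysis and ANCOVA are both unbiased under randomisation, and leaving out stratification factors makes the test conservative, not invalid. The size of the gain rests on an unstated r: at 0.9 it is 5% of the variance and no visible power. The article is also condensed, and a fuller plan may list covariates.

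Most of this stands, and it limits the point to efficiency. It does not remove the point, because the article does more than stay silent: it names the analysis model, and that model has neither a baseline covariate nor the stratification factors.

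A reader might infer four stronger criticisms. The article does not support them.

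- **That the analysis ignores baseline.** It does not: Step 1 shows that the interaction is the comparison of changes from baseline.
- **That the Tukey step compares the six group-by-time cell means, so that none of the 15 pairs is a difference in change between arms.** This is one common way to run such a test, but the sentence does not name its target. Tukey comparisons of the three arms' changes fit it equally well. The Discussion also announces both within-arm and between-arm analysis, so Pre-Post comparisons within an arm would be a declared aim.
- **That Pre and Post are treated as independent observations.** That would be serious: at r = 0.7 with the Step 3 means, simulated power falls to 2%, against 49% for the repeated-measures test. The article calls the design repeated measures, which speaks against this reading.
- **That a stratification factor is dropped by omitting centre.** Centre is not a stated stratification factor, so a centre term is an option and its absence is no inconsistency.

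**Conclusion.** The point holds as one of precision, not validity. The group-by-time test is a sound comparison of change scores, but it lacks adjustment for the outcome's baseline and for the three factors on which randomisation is stratified.

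Baseline adjustment would reduce the variance of a between-arm difference by about 25% at r = 0.5, 15% at 0.7, 10% at 0.8 and 5% at 0.9. The correlations are assumed, and equal SDs at Pre and Post are assumed for these figures. The gain is largest for outcomes with modest Pre-Post correlation and small for highly repeatable ones. The gain from FEV1, sex and age has a clear direction if they are prognostic, but no size that the article allows one to compute. No error in the Tukey step is established; its contrast only needs to be stated.

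**What to change.** Replace the two-way ANOVA sentence with an ANCOVA for each outcome, or the equivalent baseline-constrained mixed model. The Post value is regressed on arm, adjusted for that outcome's baseline, FEV1, sex and age. Centre may be added as an option.

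Report the three adjusted between-arm differences (combined v concentric, combined v eccentric, eccentric v concentric) with Tukey-adjusted 95% confidence intervals. The pairwise step then targets the between-arm effect, whatever means the present Tukey sentence intends.

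One caveat: under Physical activity and sedentary behaviour, the first accelerometer recording falls in the first week of training. For that outcome the first value is not strictly a pre-treatment baseline, which affects the change-score analysis and ANCOVA alike.

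The cost is analysis wording only. Baseline values are already collected, FEV1, sex and age are needed for randomisation, and centre is known. At 51 completers the change uses four degrees of freedom of 48, or six with centre.

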**Discussion:**

We aim to demonstrate that a combination of eccentric and concentric exercise could maximise the improvements in clinical outcomes and may be ideal for COPD patients. We also expect to unravel the molecular mechanisms underpinning muscle mass regulation after training in severe COPD patients.

*Trial Registry*: Deutshches Register Klinischer Studien; Trial registration: DRKS00027331; Date of registration: 12 January 2022. https://www.drks.de/drks_web/navigate.do?navigationId=trial.HTML&TRIAL_ID=DRKS00027331.

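### With three arms, the interaction test followed by Tukey is stricter than 5% family-wise control needs; unadjusted pairs after the same test gain power at almost no cost

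*Protocol article*

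**What the plan says.** The Statistical analysis section of the protocol article plans a two-way ANOVA of three groups by two times at a two-sided 0.05 level. Pairwise testing is conditional: "If an interaction effect is found, a Tuckey´s post hoc test will be used for pairwise comparisons".

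The Participants section sizes the trial "based on an α level of 0.05 and a power (1-β) of 0.8", using "effect sizes ranging from 0.6 to 1.2 found in similar outcomes (muscle CSA, 6MWT) in our preliminary data after eccentric training" together with a few studies of combined cycling. It concludes that "a minimum of 17 patients would be necessary per group for this study". The Molecular analyses section uses effect sizes from 1 to 2.5 with the same alpha and power, and for the biopsy subgroup "it was found that eight patients per group would be sufficient".

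Neither sample-size statement names the test, the comparison or the single effect size behind the number, and neither mentions the interaction test or Tukey's limit.

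The abstract's Discussion states the aim as a comparison between arms: "We aim to demonstrate that a combination of eccentric and concentric exercise could maximise the improvements in clinical outcomes". The section on no control and no blinding adds that both within-group and between-group analyses are intended.

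**The concern.** The trial asks which of three training modes does better, so the pairwise between-arm results are what it will report. Under the written rule, a pair must pass two hurdles that each address multiplicity: the overall interaction test, and then Tukey's limit for three means.

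With three arms, the first hurdle already does the work that Tukey would do. The second therefore lowers power for the comparisons of interest without being needed to keep the family-wise error at 5% within an outcome. The stake is avoidable loss of power in a small trial, above all for a claim that one arm beats both others. The validity of any positive finding is not at stake.

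**Working it through.** **Inputs.** From the protocol: three equal arms, measured before and after; two-sided alpha 0.05; target power 0.80; at least 17 evaluable per group (8 for biopsies); effect sizes 0.6 to 1.2 (1 to 2.5 for biopsies). Assumptions: normal errors with common variance; d is the between-arm difference in mean change divided by the SD of change; Tukey's family is the three arm means of change.

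**1. The plan's own figure.** For a two-sided, two-group t-test at 0.05 (noncentral t, df = 2n − 2, noncentrality d·√(n/2)), 17 per group gives 80% at d = 0.991 and 80.7% at d = 1.0. Eight per group gives 80% at d = 1.507. So 17 can be reproduced with an effect inside the stated range, but this d is solved back from n. Other readings also give 80% with 17 per group: the overall interaction test at d = 0.95 (one arm differs) or 1.10 (evenly spaced arms), and a paired pre-post test at d = 0.72.

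**2. The two rules, n = 17.** With two times, the interaction test equals a one-way F test on change, with df = 2 and 3(17 − 1) = 48. The pair statistic is t = (difference in mean change)/(s·√(2/n)).
- Written rule: F significant at 0.05 and |t| > q(0.95; 3, 48)/√2 = 2.418.
- Alternative: F significant at 0.05 and |t| > t(0.975; 48) = 2.011.

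Since 2.011 < 2.418, the alternative rejects every pair that the written rule rejects.

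**3. Error control of the alternative.** There are three pair hypotheses. If any two hold, all three arms are equal, so the only intersection is the overall null, which F tests at 0.05. If the arms are not all equal, at most one pair is truly null, and it is tested at 0.05. By closed testing the family-wise error is therefore at most 5%. Simulation agrees: about 5.0% under the complete null and at most about 5.0% for a single remaining null pair with the third arm shifted by up to 3 SD. Under the written rule that remaining null pair is rejected about 2% of the time.

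**4. Power at n = 17, d = 0.99** (simulated; the named pair differs by d)

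| Claim | Unadjusted, no interaction test | Tukey alone | Written rule | Alternative |
|---|---|---|---|---|
| Named pair, third arm midway | 81% | 68% | 66.5% | 70% |
| Named pair, third arm equal to one of the pair | 81% | 68% | 67.5% | 76% |
| One arm beats both others by d | 70% | not computed | 54% | 69% |

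The drop from 81% to 68% comes from Tukey. Adding the interaction test costs only a further 0.4 to 1.5 points. In the midway case the alternative gains little, because the interaction test itself then has only 71% power and becomes the limiting step.

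**5. Biopsy subgroup, n = 8, d = 1.507.** Named pair: 67% to 68% under the written rule, 70% to 77% under the alternative.

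**6. Can the written rule reach 80%?** Yes. For a named pair with 17 per group it does so at d of about 1.13 (third arm equal to one of the pair) to 1.14 (midway), inside 0.6 to 1.2. With 8 per group it does so at about 1.70 to 1.72, inside 1 to 2.5. Across the stated range at 17 per group it runs from about 25% (d = 0.6) to 85% (d = 1.2).

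**The case against.** The strongest reply is that nothing in the written rule is invalid. ANOVA followed by Tukey is conventional, controls the family-wise error and supplies simultaneous intervals. With many outcomes, some readers will prefer the stricter rule. All of that stands. It does not alter the fact that, for the three between-arm contrasts, the alternative meets the same 5% limit per outcome and never rejects less. Neither rule addresses multiplicity across outcomes.

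A second reply is that the family for Tukey's test is not spelled out. After an interaction in a 3 × 2 design it could be the six cell means, and within-group comparisons are also intended. This stands as a limit on the argument: the closed-testing result covers only the three between-arm contrasts of change.

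A reader might also infer that the stated 80% is false and is really 67%. The documents do not support this. The value d = 0.99 is not in the protocol, 17 per group fits several tests, and the written rule itself reaches 80% within the stated range. The basis of the calculation may also be set out in a full protocol or analysis plan that is not shown.

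Nor should the 54% be set against the 80% as a shortfall. They concern different claims, no success rule requiring two wins is stated, and even unadjusted tests with no interaction test give only 70% for that claim.

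**Conclusion.** The point holds as an inexpensive improvement to the analysis and is not an error in the stated power. For between-arm comparisons of change in three arms, Tukey after a significant interaction is more than is needed for 5% family-wise control per outcome. That conclusion needs no assumed effect size.

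The size of the gain does depend on one. At the illustrative d = 0.99 with 17 analysed per group, it is about 3 to 9 points for a named pair and about 15 points for one arm beating both others. Most of the written rule's loss comes from Tukey, so dropping the interaction test while keeping Tukey would recover almost nothing.

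**What to change.** - **Statistical analysis:** keep the group-by-time interaction as the precondition. Replace Tukey's test by the three between-arm comparisons of change, each at two-sided 0.05. State that with three arms this closed procedure controls the family-wise error at 5% per outcome, that it applies only to these three contrasts, and that within-group changes are reported descriptively.
- **Participants and Molecular analyses:** name the comparison and the effect size assumed, and give the power for the between-arm rule actually used. If Tukey is kept, compute the power for that rule. No particular figure, such as 67%, should be written in unless d = 0.99 is the effect that was assumed.

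The cost is a sentence or two in the analysis section and a recomputed power statement, with no added patients or measurements. The real downside is that Tukey's simultaneous intervals give way to ordinary 95% intervals for each pair.
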